### Blinding and protection against sources of bias

The following steps will be taken to reduce the risk of bias in this study: (1) The study is designed to ensure that the risk of contamination between clinic clusters is low as women are unlikely to move from clinics using PHQ-2 and those that are not, due to their geographical spread and because there will be no publicity regarding the use of PHQ-2 in some clinics. (2) Outcome assessors at the women’ homes are not involved in screening women at the clinics, and are blind to whether women received care in PHQ-2 clinics or not.

### Data collection and quality control

Quality control of field work will be implemented by research supervisors and this includes random checks on the quality of interviews (conducted by physically observing at least 10% of the interviews conducted by a research assistant). Supervisors will also work with the Data Manager to check that research assistants have correctly captured study data.

### Data protection

All data will be kept anonymously by using codes to identify individuals. Data will be uploaded to a server located in the central office where it will be cleaned and stored. Access to the datasets is possible for members of the research team through a password-protected entry.

### Sample size

Experience from the control arm of our recently concluded randomized controlled trial of intervention for perinatal depression suggests that just over 70% recover at 6 months [32]. The control arm of that study received low intensity intervention based on the specifications of mhGAP-IG and delivered by trained PHCW. We will expect about the same rate of recovery in the current study. Prior to training, we assume a recovery rate of 55% at 6 months following delivery based on previous observations by us [19]. We think that this difference of 15% is clinically meaningful to promote changes in routine maternal care. In the said RCT, we were able to complete primary outcome data at 6 months postnatal for about 85% of the participants. We will plan to recruit about twice as many mothers after the training of the providers than before the training (that is a ratio of 2:1 following training) in order to provide more information about contextual and health system factors that help or hinder effective implementation. We estimate a sample of 167 prior to training and 334 post-training to detect a difference of 70% vs 55% (equivalent odds ratio = 1.8) with 80% power at the two-sided 5% alpha level.

The correlations between the successive pre- and post-training tests conducted for the providers during the demonstration project in the State of Osun was 0.37 and the within subject variance was 0.352 [18]. Using these values and with a projected power of 80% and Type I error of 0.05, we estimate the number required to detect a difference of 1 unit between tests scores (considered a meaningful change in the assessment tool we plan to use) to be 112. Assuming an attrition of 15%, we will need a total of 129 providers to demonstrate a meaningful change between pre- and post-training scores as well as stability of skills during refresher training on average 3 months after the first training.

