In pilot exploratory studies, we have shown that it is feasible to train non-physician primary care workers in the use of mhGAP-IG to deliver care for a range of mental health conditions, including depression [18]. In a subsequent fully-powered randomized controlled trial, women with perinatal depression, other than those with severe form of the disorder, treated by frontline providers using the basic psychological approaches described in mhGAP-IG had similar rate of remission as those treated with more intensive psychological interventions [19]. In that trial, treatment of depression according to the mhGAP intervention guidelines constituted the “enhanced care as usual” (the comparison group). There was no “care as usual” group as a second comparison group. At 6 month follow-up, two thirds of the women in the enhanced care as usual had attained remission from depression, suggesting that the mhGAP-IG might be a useful tool for scaling up care for perinatal depression by non-specialist frontline providers working in low- and middle-income countries. The availability of evidence-based guidelines and approaches for managing perinatal depression [11, 12], with proven efficacy and cost-effectiveness, has opened up the possibility of scaling up service for this disabling condition. However, information is lacking as to how these guidelines and approaches can be delivered within an integrated routine perinatal care. There is a need to demonstrate the goodness of fit of these approaches to the extant health systems of LMIC, and that these approaches can be implemented in non-specialist, indeed non-physician, health care settings that characterize primary maternal care in most of sub-Saharan Africa. It will be important to empower community midwives and primary care providers with the skills to detect and respond to mental health conditions at the maternal primary care level. While the WHO has prepared, and made available several modules of training packages, there remains the need to find skilled trainers. In LMIC, where specialists are few and often overwhelmed by the demands of providing care for the teeming numbers of people in need, such specialists lack the time to provide the necessary training for the many end users (primary care workers) to improve service delivery.

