## Methods phase four

### Participants

Consecutive women making their first antenatal visit will be screened for depression with the EPDS after their consultation with the primary care providers (Fig. 2). Women who screen positive will be invited to participate in the study. At an estimated prevalence of at least 10% and about 5% refusals, we expect to screen about 3500 women to recruit 334 women with scores at or above the cut-off level (see section on sample size determination) and consenting to participate in the study. Women who screen positive, irrespective of whether they have been identified as depressed by the PHCW, and who provide informed consent to participate will constitute Cohort Two for the study. Those who screen positive but have not been identified by the primary care workers will be advised to see the providers again and notify them of their depression status. This will be particularly so for those who score 18 or more or have suicidal ideation on the EPDS and are therefore judged to have severe depression as well as those who endorse the item on suicidality on the EPDS. This is to ensure that they get timely treatment. The providers are also required to consult with the project psychiatrist for the management of patients with serious suicidal risk.

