In the formative phase of SPECTRA, a key issue that was raised by stakeholders is how to improve the identification of perinatal depression by the trained providers. While training primary care providers is known to improve identification, available evidence suggests that, even in settings with high resources, up to 50% of women with the condition are not correctly identified. Studies have shown that the use of a depression screening instrument could aid the identification of such women [38]. In our previous trials of the effectiveness of depression treatment, we have used trained research staff to administer screening instruments to identify participants with probable depression for primary care providers to assess and make the diagnosis of depression [19, 39]. We are yet to explore the feasibility of primary care providers incorporating the use of a depression screening tool into routine patient assessment. To assess this, at the implementation phase, half of the selected clinics will be randomly assigned to routinely administer a brief depression screening tool, the 2-item Patient Health Questionnaire (PHQ-2), to all women as a part of their assessments at each antenatal and postnatal visit. Women scoring 3 or more will be further assessed using the mhGAP-IG. In addition to improving the recognition of depression, routine screening might have the potential to enable health care providers to target women who are more at risk for further evaluation and thereby saving time. Our study will provide useful information about the feasibility, acceptability and impact of this approach in the identification and treatment of perinatal depression in routine maternal care in resource-constrained settings.

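### The sample size paragraph gives the wrong odds ratio for 70% vs 55% (1.91, not 1.8), an error in the safe direction, and the two recovery rates behind it are not reconciled with the Background

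*Protocol article*

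**What the plan says.** All of this is in the protocol article.

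- **Sample size, numbers.** "We estimate a sample of 167 prior to training and 334 post-training". The ratio is 2:1 after training, and about 85% of women in the earlier trial had 6-month data.
- **Sample size, target.** The stated purpose of these numbers is "to detect a difference of 70% vs 55% (equivalent odds ratio = 1.8) with 80% power at the two-sided 5% alpha level".
- **Sample size, post-training rate.** The mhGAP-IG control arm of an earlier trial (reference 32) "suggests that just over 70% recover at 6 months", and about the same is expected here.
- **Sample size, pre-training rate.** "we assume a recovery rate of 55% at 6 months following delivery based on previous observations by us [19"].
- **Background, on the trial cited as reference 19.** Its comparison arm was also mhGAP-based care by frontline providers. At 6 months "two thirds of the women in the enhanced care as usual had attained remission from depression". The section adds: "There was no “care as usual” group as a second comparison group".
- **Methods phase four, Participants.** Cohort Two consists of "Women who screen positive, irrespective of whether they have been identified as depressed by the PHCW", provided they consent. Women the provider missed are advised to go back and report their status.
- **Discussion.** In the earlier trials (references 19 and 39) research staff screened women and passed probable cases to providers. Even in well-resourced settings "up to 50% of women with the condition are not correctly identified".
- **Study setting and Data analysis.** Women come from 20 clinics, and the recovery analysis is a mixed-effects logistic regression that allows for the hierarchical data.

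**The concern.** The rates, odds ratio, sample size and power are printed as one consistent set, and they are not: two different effects are described as equivalent. A reader cannot tell whether the design target is 15 points or 13.75 points.

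The effect size is the gap between 70% and 55%, and both ends raise questions within the article. The upper rate differs from the remission rate the Background gives for a control arm of the same description. The lower rate, for untrained care, is cited to a trial described as having no untrained-care arm. In addition, 70% was seen under trial care, whereas Cohort Two is analysed whether or not the provider recognised the depression.

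What is at stake is how a non-significant remission result would be read. If the true post-training rate is nearer two thirds, the study has materially less than 80% power, and a null result could be taken to mean that the training does not work.

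**Working it through.** **Inputs from the article:** 55%, 70%, odds ratio 1.8, 80% power, two-sided 5%, ratio 2:1, 167/334, 85% follow-up (Sample size); two thirds (Background). **Assumed, not in the article:** the design effect, the share of Cohort Two women reached by care, and a 55% recovery rate in women not reached.

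**Odds ratio.** (0.70/0.30) / (0.55/0.45) = 2.333/1.222 = 1.91. Conversely, 1.8 x 1.222 = 2.20, and 2.20/3.20 = 68.75%.

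**Reproducing 167.** Pooled-variance formula with k = 2 and p̄ = (p1 + 2·p2)/3:

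n1 = [1.960·√(p̄(1−p̄)·1.5) + 0.842·√(p1(1−p1) + p2(1−p2)/2)]² / (p2−p1)²

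- 68.75% vs 55%: p̄ = 0.6417; n1 = (1.960 x 0.5873 + 0.842 x 0.5958)² / 0.1375² = 144.4, so 145. Then 145 x 1.15 = 166.75, so **167**, and twice that is 334. Dividing by 0.85 instead gives 171.
- 70% vs 55%: p̄ = 0.65; n1 = (1.960 x 0.5842 + 0.842 x 0.5937)² / 0.15² = 120.2, so 121. Inflated, this is 140 (x 1.15) or 143 (/0.85). Neither is 167. With continuity correction it is 131, inflated to 151 or 155.

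The same section's provider calculation turns 112 into 129 for 15% attrition, which is 112 x 1.15 = 128.8 (112/0.85 would be 132). That supports the x 1.15 route. This route leaves no room for a clustering factor.

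**Power with 85% follow-up.** 167 x 0.85 = 142 and 334 x 0.85 = 284. The design effect of 1.18 is assumed; it reduces 142 to 142/1.18 = 120.3.

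| Cohort Two rate (vs 55%) | Unclustered | Design effect 1.18 |
|---|---|---|
| 70% | 86% | 80% |
| 68.75% | 79% | 73% |
| 66.7% | 65% | 58% |

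At two thirds vs 55%, 80% power needs 204/408 completers, or about 240/480 recruited (204/0.85).

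**Largest design effect that keeps 80% at 70% vs 55%.** 142/120.2 = 1.18.

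**Detectable difference at 80% power from 55%.** 13.9 points unclustered; 15.0 points at design effect 1.18.

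**Dilution.** If a share f is reached and recovers at 70%, and the rest recover at 55%, the Cohort Two rate is 55% + 15·f points. Unclustered, with 142/284:

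| Share reached | Rate | Power |
|---|---|---|
| 100% | 70% | 86% |
| 90% | 68.5% | 78% |
| 75% | 66.25% | 62% |
| 50% | 62.5% | 32% |

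Power crosses 80% at f of about 92%.

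**The case against.** A reader might infer that, with a wrong odds ratio and no clustering factor, the design fails to deliver its stated 80% power. The article does not support that. Sizing on 1.8 asks for more women than 70% vs 55% requires, so at the stated rates power is 86% after 15% loss, and still 80% at a design effect of 1.18. This objection stands in full.

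Other points against, and what remains of each:

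- **The route to 167 is not unique.** 121/0.85 = 143, and 143 x about 1.17 is also 167, so an unstated clustering factor is possible. That stands as a caution. But 145 x 1.15 is exact, uses the printed odds ratio and matches the provider calculation. Either way no design effect is stated.
- **Clustering may cost little.** Both cohorts appear to come from the same clinics, so between-clinic variation may partly cancel. No intraclass correlation is given, so 1.18 is only an illustration.
- **Two thirds and just over 70% may come from different trials.** They carry references 19 and 32. That these are one trial is inferred from matching descriptions. The two figures still need reconciling.
- **The 55% is already called an assumption.** True, and earlier observations need not come from a randomised usual-care arm. What remains is that the cited trial, as described, does not obviously supply the rate.
- **Dilution is limited by design.** Table 1 has mhGAP interventions instituted at Cohort Two enrolment, missed women are advised to return, psychoeducation is for every enrolled woman (Interventions), and half the clinics use the PHQ-2. The Discussion figure is an upper bound on missed cases. Nor is the research-staff screening described there cited to reference 32. So low shares reached, such as 50%, cannot be read as forecasts.

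**Conclusion.** The odds ratio is wrong: 70% vs 55% is 1.91, and 1.8 corresponds to 68.75%. The paragraph's rates, odds ratio and sample size therefore do not agree. The error is in the safe direction and costs no power at the stated target: about 86% unclustered with 142/284 completers, and about 80% at an assumed design effect of 1.18. The claim that the design falls short of 80% at its own target is not supported.

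The weaker part is the choice of rates. If the Background's two thirds applies, power is about 65% unclustered. That figure assumes the two control arms are comparable, which is plausible but inferred, and that 55% is right, for which the article shows no clear source. Dilution in Cohort Two is a real risk of unknown size: power falls below 80% if fewer than about 92% of women are reached, assuming the others recover at 55% and ignoring clinics.

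**What to change.** Restate the Sample size paragraph and keep 167/334:

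1. Give the odds ratio for 70% vs 55% as 1.91, or keep 1.8 and give the post-training rate as 68.75%.
2. Reconcile just over 70% with two thirds, say whether references 19 and 32 describe the same arm and outcome, and report power at both rates (about 86% and 65% unclustered).
3. Name the observed source of the 55%, or drop the reference 19 citation and leave it as an assumption.
4. State the design effect assumed for the 20 clinics and how attrition was applied.
5. Quote the difference the sample can detect with 80% power: about 14 points unclustered, 15 points at design effect 1.18.
6. Show dilution as a labelled sensitivity range over the share of Cohort Two reached.

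The cost is text only. No extra women are needed, and the Study status section says recruitment and 6-month assessments are complete in both cohorts. The downside is that the stated power becomes less favourable at the lower rate.

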#### Assessing knowledge retention

Approximately 6 months after the initial training, 40 of the trained PHCW, randomly selected, will receive another test to determine the level of knowledge retention, the level of drift in the acquired skills and factors that are related to retention or drift. Such factors may be the characteristics of the providers, including their level of clinical experience, post-training performance, age, or level of clinical support.

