#### Refresher training

Approximately 6 months after the initial training of frontline primary care providers, a refresher training essentially like the initial one will be provided for the PHCW in the PHQ-2-using clinics. Participants at this training will also be tested pre and post training.

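### The provider sample size of 112 (129 with attrition) does not follow from its stated inputs, and the article's sections disagree on which providers are retested and when

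*Protocol article*

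**What the plan says.** The second paragraph of Sample size takes its inputs from an earlier demonstration project. The first is a pre/post correlation of 0.37. The second is a measure of spread, given in these words: "the within subject variance was 0.352". Power is set at 80% and type I error at 0.05. The target is then introduced as follows: "we estimate the number required to detect a difference of 1 unit between tests scores". The answer given is 112. With 15% attrition this becomes 129: "we will need a total of 129 providers to demonstrate a meaningful change between pre- and post-training scores as well as stability of skills". The stability part is tied to "refresher training on average 3 months after the first training".

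Other sections describe the later testing differently:

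- Assessing knowledge retention: at about 6 months, "40 of the trained PHCW, randomly selected, will receive another test to determine the level of knowledge retention".
- Refresher training: the timing is "Approximately 6 months after the initial training of frontline primary care providers". This session, with tests before and after it, is given only to providers in the clinics using the PHQ-2. Study instruments and the Discussion put these at half of the clinics.
- Secondary implementation outcomes, under the trainees: retention of knowledge and change in attitude at 3, 6 and 12 months after training, with no subsample stated.

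The participants paragraph under Cascade training plans for at least 200 frontline workers to be trained.

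**The concern.** The article prints every input to the calculation, so the result can be checked, and 112 looks far too large for a 1-unit change when the variance is about a third of a unit squared. A gap of that size cannot be put down to rounding or choice of formula; it points to a misreported input or result.

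The Background names retention of skills, and the amount of refresher training needed, among the issues still to be settled. If the stated requirement has no basis, readers cannot judge what the retention data can show. The sections on later testing add to the difficulty, because they do not agree on the group to which the 129 would apply.

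**Working it through.** **Inputs, all from Sample size.** Correlation r = 0.37; within-subject variance v = 0.352; difference 1 unit; power 80%; alpha 0.05 (sidedness is not stated for this calculation; two-sided is used below, and one-sided gives smaller numbers); attrition 15%.

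**Attempt to reproduce 112.** For a paired comparison, n = (z_alpha + z_power)² × Var(diff) / difference², with (1.96 + 0.8416)² = 7.849.

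| Reading of 0.352 | Var(diff) | n, normal approximation | n, exact paired t |
|---|---|---|---|
| Within-subject variance: 2 × 0.352 | 0.704 | 5.5, so 6 | 8 |
| Total variance, with the correlation: 2 × 0.352 × (1 − 0.37) | 0.4435 | 3.5, so 4 | 6 |
| Variance of the change itself | 0.352 | 2.8, so 3 | 5 |
| Correlation with the wrong sign: 2 × 0.352 × (1 + 0.37) | 0.9645 | 7.6, so 8 | 10 |
| Pairing ignored: 2 × 0.352 / (1 − 0.37) | 1.1175 | 8.8, so 9 | 11 |
| The same, doubled as for a two-group total: 4 × 0.352 / (1 − 0.37) | 2.2349 | 17.5, so 18 | 20 |

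Reading 0.352 as an SD, or using a baseline-adjusted (ANCOVA) variance, gives 5 or fewer. Even the most extreme combination tried (last row, 90% power, alpha 0.01) gives 37. The figure of 112 is not reproduced.

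**Working backwards from 112.**

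- Required Var(diff) at 1 unit: 112 / 7.849 = 14.27, so SD 3.78.
- Ratio to the paired readings: 14.27 / 0.704 = 20 times; 14.27 / 0.4435 = 32 times.
- Difference that 112 would detect on the printed variance: √(7.849 × 0.704 / 112) = 0.22 units; with 0.4435, 0.18 units.

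**Attrition.** 112 × 1.15 = 128.8, which is the stated 129. To be left with 112 after 15% loss, the step is 112 / 0.85 = 131.8, so 132. Starting from 129, 129 × 0.85 = 109.65 remain, and power falls from 80% to 79.2%.

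**What it means for the pre/post comparison.** At least 200 are to be trained; 200 × 0.85 = 170, above both 112 and 132.

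**What it means for a retest of 40.** There are two branches.

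- If 112 is right and the printed variance is wrong: the standardised change is 1 / 3.78 = 0.265, and 40 providers give about 37% power by t (39% by normal approximation). If about 100 were retested, power would be about 75%. The 100 is an assumption (half of 200), since providers per clinic are not given.
- If the printed inputs are right: 40 providers detect √(7.849 × 0.704 / 40) = 0.37 units with 80% power, well below the 1 unit sought.

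**Who is retested, and when.**

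| Section | Who | When |
|---|---|---|
| Sample size | 129 providers | refresher, about 3 months on average |
| Assessing knowledge retention | 40 at random | about 6 months |
| Refresher training | providers in PHQ-2 clinics | about 6 months |
| Secondary implementation outcomes | trainees, no subsample stated | 3, 6 and 12 months |

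**The case against.** A reader might infer that the plan retests only 40 providers, or only those in half the clinics, and is therefore underpowered for retention. The article does not support that. Secondary implementation outcomes lists retention tests of the trainees at 3, 6 and 12 months without limiting them to 40 or to the PHQ-2 clinics. Sample size links the 129 to the refresher, not to the random 40, and the stated aim for the 40 is to describe retention, drift and related factors; applying a 1-unit test at 80% power to them is an extension of the text. The 37% and 75% figures are therefore conditional illustrations. This part of the objection stands.

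A second argument is that 112 may hide a simple reporting slip. As an assumption only: a variance of 3.52 in an unpaired two-group formula gives 2 × 3.52 × 7.849 = 55.3, so 56 per group and 112 in total. That is possible, but the source of the variance is not at hand and the article describes successive tests in the same providers. It would explain how the error arose; the printed derivation would still be wrong.

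Third, the stakes are modest. Provider knowledge tests belong to the process evaluation, the attrition slip is 3 providers, and the planned 200 exceed every figure at issue for the immediate pre/post change. All of this is accepted, and it limits the weight of the point without removing it. Nor is this detail that a condensed article leaves to a fuller document: the article prints the derivation in full.

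**Conclusion.** The point holds in two parts. First, 112 cannot be obtained from the stated inputs: they require about 6 to 8 providers by exact paired t, and at most about 20 on any reading tried at 80% power and alpha 0.05. One of the variance, the unit of difference or the 112 is misreported, and the article does not allow the reader to tell which. Second, the four sections conflict on retest population and timing; the clash between 3 and about 6 months for the refresher is plain on the page.

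The attrition step is wrong in form but immaterial (129 against 132, under one point of power). A shortfall for retention is not established: it follows only if 112 is right and the printed variance wrong. The pre/post comparison is safe if at least 200 are trained as planned. The primary outcomes, identification and remission in the women, do not depend on this calculation. The matter should be corrected, as an error in a secondary implementation component.

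**What to change.** - Recompute the provider requirement from the SD of the change score on the test actually used, state the scale of that test and the sidedness, and correct whichever of the variance, the unit or the 112/129 is wrong.
- Apply attrition as n / (1 − 0.15); this gives 132 if 112 stands.
- Reconcile Sample size, Assessing knowledge retention, Refresher training and Secondary implementation outcomes, so that one statement gives which providers are retested, at which times, and whether each test falls before or after the refresher.
- Restate the power or precision that the resulting retention sample gives, separately from the immediate pre/post comparison.

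The cost is a recalculation and a few lines of text. Study status reports that the cascade training is complete, so this is a correction to the stated basis and does not change the number trained. The possible downside is a less favourable statement for retention, if 112 proves to be the correct figure and the retest is confined to a subsample.

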In an earlier study, we have demonstrated the impact of a cascade training format for the mhGAP-IG, (where mental health specialists (designated as Master Trainers) train non-specialist physicians and senior nurses (Trainers) who in turn deliver training to other primary care providers) in increasing the recognition and care for mental disorders in primary care [20]. Over the course of 12 months post-training, there was an average of 400% increase in the proportion of patients attending the clinics who received a mental, neurological or substance abuse (MNS) diagnosis [20]. There is a need to provide more robust evidence for the utility of this approach for scaling up care for mental health in routine primary care in this and other resource constrained settings.

Specifically, there are outstanding issues that require attention. First, there is a need to more closely study factors that may facilitate or impede a sustainable approach to training primary care providers to use mhGAP-IG as a clinical support tool for the delivery of effective intervention for mental health conditions in routine practice at the primary care level. Second, it is important to demonstrate whether the skill acquired following training is retained beyond the immediate post-training period and what factors affect skills retention. Complementary to this is the need to evaluate what level of refresher training might be required to sustain the clinical competence of trained primary care workers. Third, the fidelity of use of mhGAP-IG specifications need to be determined as well as factors that might affect fidelity. Fourth, the effectiveness and cost-effectiveness of recognition and treatment of mental disorders by the trained providers need to be demonstrated.

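### The provider sample is sized only to detect a 1-unit difference, yet the same calculation is said to demonstrate stability of skills, which a difference test cannot do

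*Protocol article*

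**What the plan says.** All references are to the protocol article; no separate analysis plan is at hand.

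- **Background** lists skill retention among four outstanding issues: "it is important to demonstrate whether the skill acquired following training is retained beyond the immediate post-training period".
- **Sample size** gives the correlation between successive tests and the variance ("was 0.37 and the within subject variance was 0.352"), and the error rates ("projected power of 80% and Type I error of 0.05"). From these it derives the number needed to "detect a difference of 1 unit between tests scores (considered a meaningful change in the assessment tool we plan to use) to be 112". It continues: "Assuming an attrition of 15%, we will need a total of 129 providers", and says this number serves to "demonstrate a meaningful change between pre- and post-training scores as well as stability of skills during refresher training", with the refresher placed on average 3 months after the first training.
- **Assessing knowledge retention** has 40 randomly selected trained workers who, about 6 months after training, "will receive another test to determine the level of knowledge retention, the level of drift in the acquired skills".
- **Refresher training** is at about 6 months, for workers in the PHQ-2 clinics only, with tests before and after.
- **Secondary implementation outcomes** lists retention testing at 3, 6 and 12 months, using several instruments.
- **Data analysis** does not discuss the provider tests.

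**The concern.** One calculation is offered for two opposite claims. Showing that scores rise after training means rejecting no difference. Showing that they then hold means rejecting a loss large enough to matter. The calculation addresses only the first, and nothing else in the article supplies a basis for the second. The objection is to a basis that is stated and does not fit its claim, rather than to detail that an analysis plan would normally add.

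If stability were judged by a difference test, the answer would depend on noise and numbers as much as on retention. With variable scores or few retests, a meaningful loss can be non-significant and look like stability. With precise scores, a small loss can be significant and look like failure to retain. Retention bears on how much refresher training is needed, which Background says the study should evaluate.

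**Working it through.** **Inputs from Sample size:** correlation 0.37; within-subject variance 0.352; difference 1 unit; power 80%; type I error 0.05 (taken as two-sided, since the provider calculation does not say); 112 completers; 15% attrition; 129 total. **From Assessing knowledge retention:** 40 retested.

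**1. The article's own figure.** For paired scores, n = (1.96 + 0.8416)² × Var(change) / difference². Reading 0.352 as the variance of each test, Var(change) = 2 × 0.352 × (1 − 0.37) = 0.4435, so the SD of change is 0.666. Then n = 7.849 × 0.4435 / 1² = 3.5, that is 4, or 6 with the t distribution. Other paired readings of the inputs gave at most 11, two independent groups gave 6 per group, and a test of the correlation gave 56. The 112 was not reproduced. For 112 to be right at 1 unit, the SD of change would have to be √(112 / 7.849) = 3.78. The 129 is 112 × 1.15 = 128.8; dividing by 0.85 would give 132, a small matter.

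Because 112 and its inputs disagree, the SD of change is not fixed by the article. Both values are carried forward as assumptions.

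**2. What a difference test would report** (paired t-test, two-sided 5%, noncentral t):

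| SD of change | n | True 1-unit loss: non-significant | True 0.3-unit loss: significant | 95% CI half-width |
|---|---|---|---|---|
| 3.78 | 112 | 20.7% | 13% | 0.71 |
| 3.78 | 40 | 62.8% | 8% | 1.21 |
| 0.67 | 112 | about 0% | over 99% | 0.12 |
| 0.67 | 40 | about 0% | 79% | 0.21 |

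Half-width = t × SD / √n; for example 2.023 × 3.78 / √40 = 1.21, which is wider than the 1 unit itself.

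**3. What a confidence-bound rule would report.** Declare stability only if the lower limit of the two-sided 95% CI for mean change lies above −1 unit. At a true 1-unit loss, a false claim then occurs in 2.5% of studies whatever the SD or n. With no true loss, stability is declared in:

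- 79% of studies at SD 3.78, n = 112;
- 37% at SD 3.78, n = 40;
- about 100% at SD 0.67, n = 40.

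For 80% power at SD 3.78, this rule needs 113 completers, against the stated 112.

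**4. How lenient a 1-unit margin is.** At SD 0.67 and n = 40, the rule declares stability in 99.6% of studies when the true loss is 0.5 unit and in 79% when it is 0.7.

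**5. Which retention test is meant.**

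| Section | Who | When |
|---|---|---|
| Sample size | 129 providers | refresher, about 3 months |
| Assessing knowledge retention | 40, at random | about 6 months |
| Refresher training | PHQ-2 clinics only | about 6 months |
| Secondary implementation outcomes | trainees, no number given | 3, 6 and 12 months |

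The article does not say which of these supports the stability claim, so the n = 40 figures apply only if it is the random retest.

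**The case against.** The strongest reply is that the error is a possibility and is nowhere planned. A reader might infer that the authors mean to call a non-significant difference stability; no section says so. Assessing knowledge retention, and the description of the knowledge scale under Study instruments, speak of determining or assessing drift, and estimating drift needs no margin. A decision rule for a process measure is also something a condensed article may leave to a fuller document. This stands as a limit on the finding. It does not remove the sentence in Sample size, which gives a difference calculation as the ground for demonstrating stability.

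A reader might also infer that the sample is too small for a stability claim. The figures do not support that: with a 1-unit margin, 113 completers are needed against 112. What is missing is the criterion.

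Nor can the 21% and 63% be quoted as plain facts. They rest on an SD back-calculated from a 112 that the stated inputs do not reproduce. On those inputs, a 1-unit loss would almost never be missed, and a 0.3-unit loss would count as failure only if the article's own threshold for a meaningful change were ignored.

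Two objections to the remedy also stand. The 1 unit is named as a meaningful change, not as an acceptable loss, and it is lenient if scores are precise. It is also tied to one unnamed tool, while several instruments are listed. And Study status reports cascade training and the Cohort Two 6-month postnatal assessments as complete, so provider retests may already have been done and a margin set now could be post hoc.

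**Conclusion.** The point holds in limited form. Sample size rests a claim of demonstrated stability on a calculation that can support only a claim of change, and no other section corrects it. That non-significance would be taken as stability is a risk and not a stated plan. The outcome is a secondary process measure, so severity is minor to moderate. Neither primary outcome, identification of depression or remission at 6 months, is affected.

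The size and direction of the harm depend on the SD of change. At 3.78 the danger is a missed meaningful loss; at 0.67 it is a small loss reported as failure. The article cannot settle which applies, because 112 does not follow from its inputs. Under either value the difference test answers the wrong question. These figures assume paired analysis, a two-sided 5% level and, for n = 40, that the random retest is the one meant.

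**What to change.** 1. In Sample size, limit the difference-test basis to the gain from before to after training.
2. For retention, report the mean change (retention test minus immediate post-training test) with its 95% CI. Claim stability only if the lower limit excludes a loss of 1 unit, the change the article already calls meaningful, or a smaller margin that the sponsor justifies. Otherwise report retention as not demonstrated, with the estimate and interval. State that a non-significant difference is not evidence of stability.
3. State whether the margin was fixed before the retention data were seen, and for which instrument.
4. Reconcile the number, timing and clinics of the retention tests across the four sections, and name the test that supports the claim.
5. Correct or explain the 112, giving the SD of change used.

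The cost is a few sentences, with no new data. The main downside is that, if scores are as variable as 112 implies, a 40-provider retest would probably end as retention not demonstrated (37% power with no true loss). A smaller margin also costs precision: at 0.5 unit, the same SD would need 449 completers.
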